### Exclusion criteria

 ① Patients with pharyngeal discomfort caused by bacterial or viral pharyngitis

② Patient with erosive gastroesophageal reflux, laryngeal cancer, esophageal cancer, gastric cancer, and other diseases revealed by upper gastrointestinal endoscopy or laryngoscopy

③ Patients with a history of esophageal or stomach surgery and neck radiotherapy

④ Patients with severe liver, kidney, and other organ dysfunctions and are unable to tolerate medications or allergic to medications

⑤ Patients receiving proton pump inhibitor therapy or other research drugs in the previous month

⑥ Patients who are pregnant or breastfeeding

⑦ Patients with RSI scale score (excluding the ninth item) < 10 points

⑧ Patients taking clopidogrel or warfarin

⑨ Patients contraindicated to undergo TEAS because of the following: skin rash or local infection or implantation of a pacemaker or defibrillator, electrode pads causing skin allergies or itching, acute diseases, infectious diseases, malignant tumors, cardiovascular and cerebrovascular diseases, and other malignant diseases

### Randomization and allocation concealment

We will randomize the patients according to the order of the random number table generated by the Statistical Package for the Social Sciences (SPSS) version 23.0 (IBM Corporation, New York, USA). Seventy participants will be divided into an intervention group and a control group at a ratio of 1:1. The statistician in charge of randomization will not participate in the evaluation, treatment, and result analysis of this study to ensure that the baseline RSI scores of each group are balanced. Those who will not be involved in opening the envelope in advance will put the random treatment allocation plan in a set of sealed envelopes. Each envelope must be numbered (to be able to identify all envelopes at the end of the study), opaque (to prevent transparency and visibility under strong light), and in other ways to prevent cheating. When randomizing a participant, his/her name and number on the next unopened envelope in front of the second staff member will be first recorded. Both staff members will sign the envelope, open it, and assign the grouping scheme contained therein to the participants and record this. Because it is difficult to design a placebo control for TEAS, blinding will not be used during the trial. Both the participants and outcome assessors will be aware of the grouping scheme. Statisticians who are blinded to group allocation will be responsible for analyzing the data.

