### Statistical methods

#### Sample size

According to the previous literature on the use of PPI therapy in the Chinese population [38], after 3 months of LPRD treatment, the RSI score was approximately 11.7 points, and the standard deviation was approximately 6. We will estimate that the RSI score of the intervention group will be 4.5 points higher than that of the control group after treatment. Comparing two independent samples using a two-tailed *t*-test with an alpha value of 0.05% and 80% power, a sample size of 29 patients will be obtained. Considering a dropout rate of 10%, 33 patients will be recruited for each group. In actual recruitment, we will plan to recruit 35 participants for the intervention and control groups. We will plan to recruit sufficient participants by posting posters in ENT clinics for 4 months.

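### Keeping the randomising statistician separate cannot ensure balanced baseline RSI; the claim should go, and RSI should be analysed with adjustment for baseline

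*Protocol article*

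**What the plan says.** The section on randomization and allocation concealment describes the allocation in three steps. First, the list: "We will randomize the patients according to the order of the random number table generated by" SPSS version 23.0. Second, the ratio: "Seventy participants will be divided into an intervention group and a control group at a ratio of 1:1". Third, the delivery: numbered, opaque, sealed envelopes opened in sequence before two staff members.

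Between these steps the section says that the statistician in charge of randomisation will have no part in evaluation, treatment or analysis, and gives the purpose: "to ensure that the baseline RSI scores of each group are balanced". As written, balance of baseline RSI is the purpose of the separation, and the separation is the means to it.

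RSI is the primary outcome. The abstract and the outcomes section describe it as change in score, assessed at baseline and at 4, 12 and 24 weeks. For continuous variables, the statistical analyses section names a t-test or a Mann–Whitney U test. It mentions no baseline covariate.

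**The concern.** The stated means cannot produce the stated result. A statistician who takes no part in treatment, assessment or analysis cannot steer patients into arms or shape the results, and that is worth having. But it leaves the spread of baseline RSI between arms to chance. A random list balances a baseline variable in expectation only. Closer balance in a particular trial needs a restriction that uses the variable, such as stratification or minimisation, and the article describes none.

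Two things are at stake. The first is credibility: readers of an open-label trial whose outcome assessors know the allocation will look closely at baseline comparability, and the article promises them something its described design does not deliver. The second is the estimate: a chance difference in the baseline of the primary outcome passes in part into an unadjusted comparison, and the promise of balance may make adjustment look unnecessary.

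**Working it through.** **Inputs**
- Patients per arm: 35 (randomization and sample size sections).
- SD of RSI: about 6, after treatment: "the RSI score was approximately 11.7 points, and the standard deviation was approximately 6". No baseline SD is given, so 6 is used as an assumption, with a range of 4 to 8.
- Planned difference: 4.5 points (sample size section).
- Correlation r between baseline and follow-up RSI: not given. Assumed 0.5, with a range of 0.3 to 0.7.

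**The plan's own figure.** The article gives no figure for baseline balance; its only related calculation is the sample size. With a difference of 4.5 and SD 6, the standardised effect is 4.5/6 = 0.75. A two-sided t-test at 0.05 with 80% power needs 28.9, so 29 per group, and 29/0.9 = 32.2, so 33 after 10% dropout. Both match the article. (The alpha is printed there as 0.05%; that is a separate matter and does not affect this point.)

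**Size of chance imbalance.** For two arms of 35, the standard error of the difference in mean baseline RSI is SD × √(2/35), and the 95% range is ±1.96 × SE. Normal tail areas give the probability of a difference of at least 2 points.

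| Assumed baseline SD | SE | 95% range | P(at least 2 points) |
|---|---|---|---|
| 4 | 0.96 | ±1.9 | 0.04 |
| 5 | 1.20 | ±2.3 | 0.09 |
| 6 | 1.43 | ±2.8 | 0.16 |
| 7 | 1.67 | ±3.3 | 0.23 |
| 8 | 1.91 | ±3.7 | 0.30 |

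Even a real restriction would not ensure balance. In a simulation of 20,000 trials at SD 6, with two strata split at the middle of the RSI distribution and blocks of 4, the standard error fell to about 0.88 and P(at least 2 points) to about 0.02. Both are smaller, but neither is zero.

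**How much reaches the estimate.** With equal SDs at baseline and follow-up, a baseline difference d shifts the expected between-group difference by:
- final scores: r × d
- change scores: (r − 1) × d

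For d = 2 and r = 0.5 these are +1 and −1 point, and 1/4.5 = 22% of the planned difference. For r from 0.3 to 0.7, the final-score shift runs from 0.6 to 1.4 points and the change-score shift from −1.4 to −0.6. Analysing change therefore does not remove the effect; it reverses its sign.

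**What adjustment gains.** Relative to the final-score variance, the variance of the estimated difference is 1 for final scores, 2(1 − r) for change scores and 1 − r² for ANCOVA (large-sample approximation). At r = 0.5 these are 1, 1 and 0.75. At SD 6 the standard error falls from 1.43 to 1.43 × √0.75 = 1.24 points.

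**The case against.** The strongest reply is that this is one loosely worded clause. Chance imbalance does not bias a randomised comparison or inflate the type I error, because the standard error of the t-test already allows for it. That is correct. A reader might infer from the misstatement that the trial's primary result would be biased, or that a 2-point imbalance would enter in full against the 4.5-point target. The documents support neither inference: the carry-over is partial, and it averages to zero over repeated randomisations.

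A second reply is that the lack of stratification is read from silence. This also stands. A journal article condenses the full protocol, which may contain a restriction on RSI. But the rationale printed here would still be wrong, because it credits the separation of the statistician with the balance.

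Two other readings are tempting. One is that the arms may come out unequal in size. The article plans 35 per group with a prepared set of envelopes, so a list of fixed total is the natural reading, and nothing indicates otherwise. The other is that someone will use RSI to steer allocation. Nothing in the text says so, and a stratified scheme that used RSI would still be random.

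Finally, baseline adjustment is commonly left to the analysis plan. Its absence is therefore not charged as an omission. The point is that the article does name a method, and a better one is available from data already collected.

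**Conclusion.** The point holds in a limited form. The article attributes to its design a property that the described steps do not have: nothing in them acts on baseline RSI, so balance is not ensured. The expected chance difference is moderate, with a 95% range of ±1.9 to ±3.7 points and a 0.04 to 0.30 probability of at least 2 points, over assumed baseline SDs of 4 to 8. Entry criteria bound baseline RSI from below, so its SD may well differ from the post-treatment 6; no value in the range makes balance certain. The consequence is lost precision and a misleading assurance. The validity of the test is not affected. The carry-over of about 1 point for a 2-point imbalance rests on the assumed correlation of 0.5 and equal SDs. These figures describe a list without restriction on RSI. If one exists and is simply not described, the imbalance would be smaller, and what remains to correct is the description.

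**What to change.** 1. In the randomization section, delete the clause on balanced baseline RSI and let the separation of the statistician stand as a safeguard against bias. If a restriction on RSI was in fact used, describe it and include it in the analysis model.
2. In the statistical analyses section, replace the unadjusted two-group test for RSI with ANCOVA: RSI at follow-up (or its change) on treatment group and continuous baseline RSI. With baseline as covariate, final score and change give the same treatment effect.

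The cost is one deleted clause and one covariate. Baseline RSI is already measured before treatment starts, so no new data are needed. The model assumes a roughly linear relation with baseline, which should be checked.

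Replacing the list with stratified blocks is not recommended. According to the trial status section, recruitment began on June 1, 2021 and was due to end on October 1, 2021. A change of list during that period, in an open-label trial where blocks add some predictability, costs more than this point warrants.

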### Interventions

For patients diagnosed with LPRD, we will conduct diet and lifestyle education, including quitting smoking and alcohol, low-fat diet, fasting 3 h before going to bed, and avoiding spicy fried, coffee, and carbonated drinks. The control group will receive conventional PPI acid suppression treatment, omeprazole 20 mg bid orally, and the intervention group will be treated with TEAS for 12 weeks on this basis. Because LPRD requires long-term treatment and takes into account the time barriers required for patients to frequently return to the hospital, most of the treatments are performed at home by the patients. Participants can easily identify whether the electrotherapy device is turned on and whether it is performing effective electrical stimulation. Thus, it is difficult to set blind methods in this experiment.

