#### Secondary outcomes

The reflux finding score (RFS) is a widely used scale [32]. According to the results of laryngoscopy, it assesses whether there are signs of vocal cord edema, granuloma in the larynx, posterior hyperplasia, mucosal hyperemia, or erythema. The total RFS score ranges from 0 to 29. Patients will be instructed to undergo laryngoscopy before treatment and 4 and 12 weeks after treatment to objectively assess the changes in reflux signs.

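### RFS is graded by assessors who know the allocation, although the reasons given for not blinding apply only to participants; masked grading of laryngoscopy was available and cheap

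*Protocol article*

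**What the plan says.** Under Randomization and allocation concealment, the protocol article gives its reason for an open trial: "Because it is difficult to design a placebo control for TEAS, blinding will not be used during the trial". It then applies this to everyone who measures an outcome: "Both the participants and outcome assessors will be aware of the grouping scheme". The only people kept unaware are those who run the analysis: "Statisticians who are blinded to group allocation will be responsible for analyzing the data".

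The Interventions section adds a second reason: "Participants can easily identify whether the electrotherapy device is turned on and whether it is performing effective electrical stimulation".

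Under Secondary outcomes, RFS is a grading of visible signs: "According to the results of laryngoscopy, it assesses whether there are signs of vocal cord edema", followed by granuloma, hyperplasia and redness. "The total RFS score ranges from 0 to 29". Laryngoscopy is done before treatment and at 4 and 12 weeks, and its stated purpose is "to objectively assess the changes in reflux signs". No section makes an exception for the person who grades RFS.

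**The concern.** Both reasons for leaving the trial open describe what the patient perceives. They justify unblinded participants and, in practice, unblinded treating staff. They say nothing about a reader who looks at an image of a larynx, so the open status of the RFS assessor does not follow from them.

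This matters because the other scored outcomes offer no protection. RSI is a patient questionnaire, and LPR-HRQL and the throat-pain scale also record the patient's own experience. All three come from people who know whether they have the device. RFS is one of only two efficacy measures that do not depend on self-report. The other is Dx-pH monitoring, done at baseline and week 12, and the article itself reports that in earlier studies most patients did not want to repeat that test. If the RFS grader also knows the arm, agreement between RSI and RFS is weak corroboration, since expectation could move both in the same direction.

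**Working it through.** **Step 1: do the stated reasons cover the RFS assessor?**

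| Reason in the article | Whom it prevents from being masked | Does it prevent masked reading of a laryngoscopy? |
|---|---|---|
| A TEAS placebo is hard to design (Randomization and allocation concealment) | Participants | No |
| Participants can tell whether the device is on and stimulating (Interventions) | Participants | No |

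The statement on assessors is explicit and unqualified. It is a stated choice, so a fuller document cannot be presumed to reverse it.

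**Step 2: when does the exposure arise?** RFS may serve as an entry criterion, and the first laryngoscopy precedes treatment. A score given for eligibility cannot be influenced by an allocation made later. The exposed gradings are those at weeks 4 and 12.

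**Step 3: how much could it matter?** The article gives no RFS standard deviation, no expected RFS difference and no estimate of assessor bias, so there is no stated RFS figure to reproduce. The sample size calculation concerns RSI only. What follows is an illustration in SD units.

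Inputs:
- n per arm: 35 (Sample size). With the planned 10% dropout, 35 × 0.9 = 31.5, taken as 31.
- Two-sided significance level 0.05, t-test (Statistical analyses).
- True treatment effect on RFS: zero (assumed).
- Systematic scoring shift between arms, *b*, in SD units: 0, 0.1, 0.25 and 0.5 (all assumed).

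Formula: the t statistic has df = 2n − 2 and noncentrality λ = b × √(n/2). The false-positive rate is P(|T| > c), where T is noncentral t and c is the two-sided 5% critical value.

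- n = 35: df = 68, c = 1.996, √(35/2) = 4.183
- n = 31: df = 60, c = 2.000, √(31/2) = 3.937

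| Assumed shift *b* | λ, n = 35 | False-positive rate, n = 35 | λ, n = 31 | False-positive rate, n = 31 |
|---|---|---|---|---|
| 0 | 0 | 5.0% | 0 | 5.0% |
| 0.1 SD | 0.418 | 7.0% | 0.394 | 6.7% |
| 0.25 SD | 1.046 | 17.8% | 0.984 | 16.2% |
| 0.5 SD | 2.092 | 54.1% | 1.969 | 49.1% |

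A small shift does little harm and a moderate one does a great deal. Nothing in the article shows where in this range the trial would fall.

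**The case against.** The case on the other side has real force in several places.

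- **RFS is secondary and the choice is disclosed.** The primary outcome is self-reported, so masking the RFS grader leaves the main bias of this open trial untouched. The Discussion also names the lack of blinding as a limitation. This stands, and it limits the weight of the point. It does not answer it: the Discussion speaks of blinding in general and does not recognise that RFS could have been masked without a sham device.
- **RFS is not the only possible check.** A reader might infer that every efficacy measure can be moved by expectation. The article does not support that. Dx-pH monitoring is an instrument measurement and a secondary outcome at week 12. It is an imperfect check because of the expected reluctance to repeat it, but it exists.
- **The word objective may be over-read.** It can mean signs seen by a clinician as opposed to symptoms reported by a patient. That is a fair reading, and the article does not claim masked grading. The bias does not depend on the word.
- **Knowledge of visit.** A reader might infer that assessors are stated to know the visit as well as the arm. The article speaks only of the grouping, so the point is confined to arm.
- **The shifts are assumed.** This stands fully. The percentages show sensitivity and do not predict what will happen.
- **Recruitment had begun.** Trial status gives a first patient on June 1, 2021, before protocol version 2.0 of July 10, 2021. Some early examinations may have no stored recording. This limits what the fix can recover but does not remove its value for the remaining visits.

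**Conclusion.** The point holds as an avoidable weakness in a secondary outcome. The plan leaves the RFS grader aware of allocation for reasons that apply to participants alone, and so exposes the week-4 and week-12 RFS comparisons to observer bias that could cheaply be reduced.

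Its size cannot be fixed from the article. Under the assumptions of no true effect, a t-test at two-sided 0.05 and a systematic shift of 0.1 to 0.5 SD, the false-positive rate for RFS runs from about 7% to 54% with 35 per arm, and from about 7% to 49% with 31 per arm.

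A reader might go further and conclude that the trial's main result is undermined by this choice, or that a false-positive rate near the upper figures is likely. Neither follows. The primary RSI is self-reported and is unaffected by who reads the laryngoscopy, and no document supplies evidence on the size of assessor bias. The point is worth acting on because the remedy is inexpensive.

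**What to change.** Amend Randomization and allocation concealment as follows.

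- Outcome RFS is graded from stored, coded laryngoscopy recordings, in mixed order and masked to arm. The grader is a member of the existing team, preferably one who did not perform that patient's examination. Another existing team member holds the code.
- RFS used for eligibility can still be scored at the visit.
- The text states that RFS grading is masked while participants, treating staff and other assessments remain open. It should not say that only patients and treating staff are unblinded, since nothing in the article masks those who classify adverse events or handle Dx-pH monitoring.
- Any early visit without a stored recording is reported as graded unmasked.

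**Cost.** Up to 70 patients × 3 examinations = 210 recordings to store and code, with no extra reader, procedure or visit and no change to the sample size. It assumes that the clinic can store laryngoscopy images. Some early recordings may already be lost, and masking is imperfect if the grader recognises a recording. The change does not reduce bias in RSI.

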### Interventions

For patients diagnosed with LPRD, we will conduct diet and lifestyle education, including quitting smoking and alcohol, low-fat diet, fasting 3 h before going to bed, and avoiding spicy fried, coffee, and carbonated drinks. The control group will receive conventional PPI acid suppression treatment, omeprazole 20 mg bid orally, and the intervention group will be treated with TEAS for 12 weeks on this basis. Because LPRD requires long-term treatment and takes into account the time barriers required for patients to frequently return to the hospital, most of the treatments are performed at home by the patients. Participants can easily identify whether the electrotherapy device is turned on and whether it is performing effective electrical stimulation. Thus, it is difficult to set blind methods in this experiment.

### Transcutaneous electrical acupoint stimulation

A household intermediate frequency pulse electrotherapy instrument (JF-ZP-YY01, Tianchang Jianfa Ziran Medical Products Co. Ltd, Chuzhou, China) with a pulse width of 280 us ± 10% will be used for TEAS in this trial. It has two 1.2 kHz ± 10% output channels and different stimulation intensities. The stimulation intensity can be adjusted according to each individual’s feeling. The stimulation intensity should be gradually increased to the maximum stimulation threshold without feeling pain or discomfort. The intermediate-frequency pulse electrotherapy instrument is easy to operate. The first operation is performed in the outpatient treatment room. Professional Chinese medicine physicians will guide the patient and observe whether there are adverse reactions during the first treatment. The participants will be instructed to record the treatment diary and record the operation time.

According to the previous literature, we will use the following three acupoints for the treatment of LPRD [23–25]: *Tiantu* (RN22), *Renying* (ST9), and *Neiguan* (PC6) (Table 1 and Fig. 1).

**Table 1 Tab1:** Locations of acupoints in intervention group

Acupoints	Locations
*Tiantu* (RN22)	Located on the neck, the current midline, in the center of the suprasternal fossa, between the left and right sternocleidomastoid muscles
*Renying* (ST9)	In the neck, next to the laryngeal junction, the front edge of the sternocleidomastoid muscle, the common carotid artery
*Neiguan* (PC6)	On the palm side of the forearm, two cun^a^ above the transverse crease of the wrist, between the palmar longus tendon and the flexor carpi radialis tendon

^a^1 cun (≈ 20 mm) is defined as the width of the interphalangeal joint of patient’s thumb

**Fig. 1 Fig1:**
[figure not shown]
Locations of acupoints. **a**
*Tiantu* (RN22) and *Renying* (ST9) on the left. **b**
*Tiantu* (RN22) and *Neiguan* (PC6) on the left

Traditional Chinese medicine believes that LPRD is a syndrome of deficiency of the essence and deficiency of yin. It is often based on qi deficiency and yin deficiency, with Qi stagnation, phlegm dampness, phlegm fire, cold, and heat as the standard. Disorders of the spleen, stomach, liver, and gallbladder are the main causes of this disease. The main principles of treatment are to regulate qi and relieve depression, resolve phlegm, reduce adversity, nourish yin and clear fire, and invigorate the spleen and stomach [26]. Wang et al. showed that acupuncture at RN22 and PC6 acupoints combined with esomeprazole tablets and that mosapride tablets is more effective than Western medicine alone [23]. Zhang et al. reported that acupuncture at the RN22 point combined with omeprazole can achieve satisfactory results in the treatment of reflux disease of the throat [24]. The therapeutic effect of acupoint injection at RN22 combined with electroacupuncture at the ST9 acupoint is better than that of oral drugs in the treatment of chronic pharyngitis [27].

The first group will consist of RN22 and ST9 acupoints on one side, and the second group will consist of RN22 and PC6 acupoints on one side. Each group will be treated for 15 min; after one side will be completed, the contralateral two groups will be treated. Therefore, one treatment will be 60 min in total, once a day, five times a week. The patient will be instructed not to increase or decrease the number of treatments.

Every patient in the intervention group will receive the instruction manual of the instrument and the detailed treatment plan. The treatment will be mainly performed at home and will be completed by the patient. The first treatment will be performed in the outpatient department of the Otolaryngology Department, guided and demonstrated by professional Chinese medicine physicians. In the initial treatment stage, the patient will be instructed to take photos and provide feedback to ensure that the patient chooses the correct acupoints. For patients with operational problems, we will arrange professionals to provide telephone and video guidance. In addition, we will record a video of the treatment steps to ensure that the patient understands the location of the acupoints and the treatment steps.

